#### Group difference in dynamic glutamate response induced by cognitive task (Aim 2)

To directly test our hypothesis of an elevated dynamic glutamate response to cognitive tasks, dynamic glutamate response will be compared among the four groups using ANCOVA. In addition, dynamic glutamate response provides another measure of neural activity, which is considerably less sensitive to vascular changes. Establishing these differences will enable us to further elucidate NVC abnormality in ME/CFS. Bivariate correlations will be tested between the dynamic glutamate responses and health scores. In addition, the extent to which these correlated responses explain variance in the health scores after accounting for all other variables will be evaluated using hierarchical regression.

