Additional brain area recruitment associated with cognitive tasks during task fMRI is one of the most frequently observed differences between patients with ME/CFS and controls (4). The task fMRI signal was based on neurovascular coupling (NVC), the dynamic regulation of blood flow induced by neural activity. NVC is a critical process for normal brain function, in which glutamate from an active neuron stimulates Ca^2+^ influx in adjacent neurons and astrocytes. In turn, increased Ca^2+^ concentrations in both astrocytes and neurons trigger the synthesis of vascular dilation factors to increase local blood flow, ensuring activated neurons are supplied with their energy needs (5, 6). Previous genetic and electrophysiological studies showed that transient receptor potential melastatin subfamily 3 (TRPM3) activity and Ca^2+^ mobilization were reduced in ME/CFS (7–9). Reduced Ca^2+^ mobilization may delay NVC and result in the less responsive fMRI signals (i.e., coupled less tightly with tasks with lower sample entropies) that were observed in our previous neuroimaging study (10). The delayed NVC ensues subtle brain changes, culminating in chronic brain injury and associated cognitive impairment (5), presenting as structural changes in brain regions (11–16) susceptible to hypoxia. Moreover, we postulate that a higher level of glutamate is released because of delayed NVC in ME/CFS patients and results in additional brain area recruitment during tasks (4, 10). Excess glutamate may cause excitotoxicity, which is consistent with increased expression of the vasoactive intestinal peptide receptor 2 observed in ME/CFS (17). The intestinal peptide receptor 2 is a neuroprotective agent against excitotoxicity and is released in response to high levels of glutamate (18). Thus, we hypothesize that delayed NVC may explain hypoxia-related brain structural changes and excess glutamate in ME/CFS, which further impairs the brain because of excitotoxicity.

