#### Group difference in hemodynamic response function (HRF) (Aim 1)

The HRF features will be compared using one-way analysis of covariance (ANCOVA) among the four groups. The respiration response function (RRF) will be modeled in the breath-holding tfMRI data. This will enable us to disentangle non-neuronally-induced cerebrovascular reactivity from the neurovascular coupling effects. The RRF will be summarized similarly to the HRF by amplitude (*H*), time to peak (*T*), onset (*O*), and width (*W*). The RRF features at the same brain location will be used as a covariate in the HRF ANCOVA analysis to exclude confounding cerebrovascular reactivity (e.g., RRF-*H* as a covariate for HRF-*H* comparison, etc.,). Group differences in each RRF feature will also be tested using ANCOVA among the four groups. The bivariate correlation will be tested between the HRF/RRF features and the health scores. Additionally, the extent to which these correlated features explain variance in the health scores after accounting for all other variables will be evaluated using hierarchical regression.

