### Power analysis

The HRF features and dynamic glutamate changes associated with a cognitive task in individuals with fatigue and ME/CFS will be tested for the first time. Therefore, there are no preliminary results on these two groups' variances and means of these measures. This study's total sample size (*N* = 288) was determined to detect the effect size of 0.25 (Figure 4). For the same reason, the learning curve for neuromarker identification cannot be determined. However, one previous study determined that a test sample size of 100 would be needed to test a classifier to achieve reasonable precision in the validation (38).

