**Figure 4 F4:**
[figure not shown]
Power analysis. The theoretic sample size was determined by the sensitivity value (effect size = 0.25) that further decreasing the effect size from 0.25 to 0.2 requires appreciably increasing the sample size from 251 to 390. The sample size assumes that 87% of data are valid (*N* = 251/0.87 ~ 288). Invalid data include MRI images with excessive motions and new conditions found after completion of the study, and the percentage was estimated empirically. The analysis of covariance (ANCOVA) will be used to determine the mean difference among four groups with 5 covariates of age, gender, activity levels, body mass index, depression, and anxiety. We assumed both type I and II errors of 0.05.

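### Aim 2 calls a four-group ANCOVA a direct test of elevated glutamate in ME/CFS, but that group test has no direction and is not specific to ME/CFS

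*Protocol article*

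**What the plan says.** **Hypothesis.** The Introduction of the protocol article is directional and concerns one group: "we postulate that a higher level of glutamate is released because of delayed NVC in ME/CFS patients". It also presents delayed neurovascular coupling (NVC) as the process in ME/CFS behind the hypoxia-related brain changes.

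**Aim 2 test.** "To directly test our hypothesis of an elevated dynamic glutamate response to cognitive tasks, dynamic glutamate response will be compared among the four groups", with ANCOVA as the method.

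**Aim 1 test.** "The HRF features will be compared using one-way analysis of covariance (ANCOVA) among the four groups". No claim of directness is made here, but the motivating hypothesis, delayed NVC, is again about ME/CFS.

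**Related text.** The data analysis plan applies a false discovery rate (FDR) correction to multiple comparisons without naming them. The section on the sample population says the fatigue and fibromyalgia groups are there to secure specificity of the neuromarker. The Figure 4 legend sizes the study on the four-group ANCOVA alone: "mean difference among four groups with 5 covariates of age, gender, activity levels, body mass index, depression, and anxiety", and "We assumed both type I and II errors of 0.05". No ME/CFS contrast and no direction is stated for the group comparisons of either aim.

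**The concern.** The four-group comparison in an ANCOVA asks whether the four adjusted means are all equal. The hypothesis asks whether one of them, ME/CFS, is higher. These are different questions. The F test can be significant because fibromyalgia or chronic fatigue stands apart while ME/CFS equals controls, or because ME/CFS is lower than controls. Since the text assigns the hypothesis to this comparison and calls the test direct, a significant F could be reported as confirmation when the data show something else. Aims 1 and 2 are both primary, so this affects the main claims of the study about mechanism.

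**Working it through.** **1. The plan's own figure.** Inputs from the power analysis and the Figure 4 legend: effect size 0.25 (read as Cohen's f, an assumption), type I and type II error 0.05, four groups. Power is P(F′ > F_crit), where F′ is noncentral F with λ = f²N.

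- With 3 numerator df, as four groups require, 95% power needs N = 279 at f = 0.25 and 434 at f = 0.20.
- The stated 251 and 390 come out exactly with 2 numerator df. At N = 251 the 3-df test has 92.5% power.
- The legend says 5 covariates but lists six. This does not change N.

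The sample size is a separate matter. What counts here is that the planned sizing refers to the omnibus test.

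**2. Inputs for the check.**

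- Valid participants: 87% of 91/61/91/45 gives 79 ME/CFS, 53 chronic fatigue, 79 healthy controls (HC) and 39 fibromyalgia, N = 250.
- Error df: 250 − 4 − 6 = 240. Two-sided alpha 0.05.
- The article gives no group means or SDs, so a shift of 0.5 residual SD and the patterns below are assumptions. Covariates are taken to cost degrees of freedom only.

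**3. Formulas.**

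- Omnibus: λ = Σ nᵢ(μᵢ − μ̄)², with μ̄ the weighted mean and F_crit(3, 240) = 2.642. If a single group k is shifted by δ, λ = n_k(N − n_k)δ²/N.
- ME/CFS v HC: noncentral t with parameter (μ_ME − μ_HC)/√(1/79 + 1/79). The standard error is √(2/79) = 0.159, and t_crit(240) = 1.970. For a difference of 0.5 the parameter is 0.5/0.159 = 3.14.

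**4. Results.**

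| True pattern (SD from HC) | λ | Omnibus F significant | ME/CFS v HC significant |
|---|---|---|---|
| Only fibromyalgia +0.5 | 39×211×0.25/250 = 8.23 | 66% | 5% |
| Only chronic fatigue +0.5 | 53×197×0.25/250 = 10.44 | 77% | 5% |
| Only ME/CFS −0.5 | 79×171×0.25/250 = 13.51 | 88% | 88%, sign negative |
| Only ME/CFS +0.5 | 13.51 | 88% | 88% |
| All three patient groups +0.5 | 13.51 | 88% | 88% |
| ME/CFS +0.5, other patient groups +0.25 | 2×79×0.25² = 9.88 | 75% | 88% |

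In the first two rows ME/CFS equals controls, yet the omnibus F is usually significant. Rows three and four have the same λ, so the F test cannot tell a higher ME/CFS response from a lower one.

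**5. Cost of sharing alpha.** If ME/CFS v HC is tested at 0.05/3 (t_crit = 2.411), its power for a 0.5 SD difference falls from 88% to 77%.

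**The case against.** **The aims speak only of group differences.** The primary outcomes are worded that way, these measures are being tested in ME/CFS for the first time, and comparing all four groups is deliberate. This stands as a reason to keep the omnibus F. It does not rescue the Aim 2 sentence, which ties the comparison to a hypothesis of elevation.

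**Follow-up contrasts may be in a fuller plan.** An article condenses, and nothing in it says that inference stops at the F test. A reader might infer that the study has no ME/CFS contrast, or that the investigators would read any significant F as an ME/CFS effect. The document supports neither. What remains is narrower: the sentence names the four-group comparison as the direct test, and that is wrong whatever follows it. The FDR sentence names no comparisons, so it does not supply the missing contrast.

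**Power.** A reader might also infer that the omnibus test wastes power against any planned ME/CFS contrast. The figures do not support that.

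- ME/CFS v HC equals the omnibus (88% each) when only ME/CFS or all patient groups are shifted. It gains only in the graded pattern.
- It can be lower. If ME/CFS and chronic fatigue are equally raised and fibromyalgia is not, it has 88.1% against 92.5% for the omnibus (overall f = 0.25, 251 valid participants).
- ME/CFS against the other three groups pooled reaches 96% when only ME/CFS is shifted by 0.5 SD, but drops to 39% when all patient groups are.

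Without stated group means, no pattern can be preferred.

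**Conclusion.** The point holds as a mismatch between the stated hypothesis and the stated test. Under the assumed 0.5 SD shift and 250 valid participants, the test called direct is significant about two-thirds to three-quarters of the time (66% and 77%) when only another patient group differs. It is significant equally often (88%) when ME/CFS differs in either direction. These percentages depend on the assumed shift and allocation. The lack of direction and of specificity does not.

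The case for change rests on interpretation and not on a general gain in power. For Aim 1 the point is weaker: the text there does not claim a direct test, but the same hypothesis about ME/CFS stands behind it.

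**What to change.** Reword the Aim 2 analysis so that, within the same ANCOVA, the 1-df contrast of ME/CFS with HC is the named test of the hypothesis, with its estimate and sign reported. Do the same for each HRF feature in Aim 1. Apply the FDR over these contrasts. Test ME/CFS v chronic fatigue and ME/CFS v fibromyalgia as secondary specificity contrasts after the primary one, and keep the omnibus F as supportive.

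The cost is wording only: same model, data and sample. There is a small downside if the specificity contrasts share alpha with the primary one, because its power then falls to about 77% at 0.05/3. Testing them afterwards avoids that.

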#### Neuromarker identification and validation (Aim 3)

The data will be randomly divided into a model group (168 samples from 51 ME/CFS, 41 fatigue conditions, 51 HCs, and 25 fibromyalgia), as well as a validation group (120 samples from 40 ME/CFS, 20 fatigue conditions, 40 HCs, and 20 fibromyalgia). The region-based HRF features, RRF features, sample entropy, and fractional amplitude of low-frequency fluctuations will be converted into whole-brain voxel-wise maps by assigning regional measures to each voxel within the region and zeros outside. Each MRI measure (GM and WM density map, HRF features, etc.) will be entered as input for least absolute shrinkage and selection operator—regularized principal components regression (LASSO-PCR) (21) to generate a brain pattern of distributed clusters that predict disease severity. The identified brain pattern will be integrated using multimodal deep Boltzmann machines (DBM) (22) as a neuromarker to predict ME/CFS. The importance of each cluster in the brain pattern will be determined by the Kullback-Leibler divergence of the prediction distributions with and without it. Clusters with no significant information gain will be removed. The receiver operating characteristic (ROC) curve of the identified neuromarker will be determined using data from the validation group.

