**Methods and analysis:**

This cross-sectional study will recruit 288 participants (91 ME/CFS, 61 individuals with chronic fatigue, 91 healthy controls with sedentary lifestyles, 45 fibromyalgia). The ME/CFS will be diagnosed by consensus diagnosis made by two clinicians using the Canadian Consensus Criteria 2003. Symptoms, vital signs, and activity measures will be collected alongside multimodal MRI.

The HRF, RRF, and glutamate changes will be compared among four groups using one-way analysis of covariance (ANCOVA). Equivalent non-parametric methods will be used for measures that do not exhibit a normal distribution. The activity measure, body mass index, sex, age, depression, and anxiety will be included as covariates for all statistical analyses with the false discovery rate used to correct for multiple comparisons.

The data will be randomly divided into a training (*N* = 188) and a validation (*N* = 100) group. Each MRI measure will be entered as input for a least absolute shrinkage and selection operator—regularized principal components regression to generate a brain pattern of distributed clusters that predict disease severity. The identified brain pattern will be integrated using multimodal deep Boltzmann machines as a neuromarker for predicting ME/CFS fatigue conditions. The receiver operating characteristic curve of the identified neuromarker will be determined using data from the validation group.

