### The recruitment and selection of the sample population

We will recruit 288 adult participants (18–65 years old), including 91 patients with ME/CFS, 61 individuals with chronic fatigue, 91 HCs with sedentary lifestyles, and 45 patients with fibromyalgia. The risk of an ill-defined ME/CFS patient cohort will be mitigated by employing a consensus diagnosis of ME/CFS from two clinicians ([name] and [name], both have over 10 years of experience in ME/CFS) and using the Canadian Consensus Criteria (CCC) 2003 (1). This study will also include groups of fibromyalgia, a frequent co-morbidity of ME/CFS. The American College of Rheumatology (ACR) 2016 fibromyalgia criteria (25) will be used for screening and followed by clinic diagnosis by a rheumatologist ([name]). The chronic fatigue is defined as self-identified ME/CFS but not confirmed by the two clinicians (i.e., present with other conditions or lack core ME/CFS symptoms) or with other disorders (not ME/CFS or fibromyalgia) that fatigue is a significant symptom. These two groups are included to ensure specificity of the identified neuromarker. Patients with ME/CFS have reduced daily activity because of their illness. However, a sedentary lifestyle itself may affect brain structure and function. Therefore, there is a risk of identifying brain structural or functional differences from ME/CFS sequelae, rather than from the illness per se. This study will mitigate against this problem by selecting HCs with sedentary lifestyles. A sedentary lifestyle will be defined as spending <60 min in moderate or high-intensity activity (i.e., exercise) per week (26). Furthermore, activity level will be monitored by the Actigraph GT3X-BT device (ActiGraph LLC., United States) for 14 days. The recorded activity level will be included as covariates for all statistical analyses but will not change participants' eligibility.

The inclusion criteria include adult individuals who express an interest, meet each group definition, and are confirmed by clinicians.

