### Progress and plan

This study commenced in January 2020. The participant recruitment commenced in August 2020 and to date (20 May 2022), we have received and processed 902 expressions of interest and recruited 110 participants.

We will start preliminary analysis in July 2022 and disseminate preliminary results in October 2022. The final results and data release will be available in 2024.

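### The Aim 3 training/validation split is stated two ways (188/100 and 168/120); both allocate all 288 recruits although about 251 are expected to be valid, and only the 120 version keeps 100 valid test cases

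*Protocol article*

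**What the plan says.** Four places in the protocol article bear on the split.

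- **Abstract, Methods and analysis.** The data are to be "randomly divided into a training (*N* = 188) and a validation (*N* = 100) group". No breakdown by group is given.
- **Neuromarker identification and validation (Aim 3).** The division is into a "model group (168 samples from 51 ME/CFS, 41 fatigue conditions, 51 HCs, and 25 fibromyalgia" and a "validation group (120 samples from 40 ME/CFS, 20 fatigue conditions, 40 HCs, and 20 fibromyalgia", with the ROC curve taken from the second.
- **Power analysis.** The article says it cannot work out a learning curve, and it supports the validation size with one earlier study, according to which "a test sample size of 100 would be needed to test a classifier to achieve reasonable precision in the validation".
- **Figure 4 legend.** "The sample size assumes that 87% of data are valid (*N* = 251/0.87 ~ 288", where the loss covers scans spoiled by motion and conditions that come to light once the study is over.

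The recruitment section sets the target at 288, "including 91 patients with ME/CFS, 61 individuals with chronic fatigue, 91 HCs with sedentary lifestyles, and 45 patients with fibromyalgia". Nowhere does the article say whether the split counts are participants recruited or participants with valid data.

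**The concern.** Both splits are current text in the same article, so one is not a superseded version of the other. Aim 3 is listed among the primary outcomes, and the article says that it publishes its analysis plan for the sake of reproducibility. With two test-set sizes on record, a later report could cite either one as planned.

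The choice also decides whether the plan meets the only justification it offers for the validation size. The cited figure of 100 is a number of cases on which the classifier is actually tested, so it has to be compared with valid cases. The plan itself expects to lose 13% of its data, and neither split mentions that loss.

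**Working it through.** **Inputs.** Splits 188/100 (abstract) and 168/120 (Aim 3 section); targets by group 91, 61, 91 and 45 (recruitment section); valid fraction 0.87 and valid N of 251 (Figure 4 legend); cited test size 100 (Power analysis).

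**1. The plan's own total.** 251 / 0.87 = 288.5, which the plan gives as about 288 (289 if rounded up). In reverse, 288 × 0.87 = 250.6, about 251. The stated figure is reproduced.

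**2. Is each split internally consistent?**
- Aim 3 section: 51 + 41 + 51 + 25 = 168; 40 + 20 + 40 + 20 = 120; 168 + 120 = 288.
- By group: 51 + 40 = 91; 41 + 20 = 61; 51 + 40 = 91; 25 + 20 = 45. All four match the recruitment targets.
- Abstract: 188 + 100 = 288.

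Each adds up, but the two differ by 20 participants in both parts.

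**3. Can the counts be met with valid data?** Both splits use all 288, against about 251 expected valid. If the counts were meant as valid cases, about 288 / 0.87 = 331 recruits would be needed, which contradicts the target of 288. If exactly 100 valid cases were set aside for validation, 251 − 100 = 151 would remain for training, not 188.

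**4. Expected valid cases (n × 0.87).**

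| Set | Allocated | Expected valid |
|---|---|---|
| Validation, Aim 3 section | 120 | 104.4 |
| Validation, abstract | 100 | 87.0 |
| Model, Aim 3 section | 168 | 146.2 |
| Training, abstract | 188 | 163.6 |

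The 120 divides by group into 40 × 0.87 = 34.8, 20 × 0.87 = 17.4, 34.8 and 17.4, or about 35 ME/CFS, 17 chronic fatigue, 35 healthy controls and 17 fibromyalgia.

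**5. Against the cited 100.** Allocation needed for 100 expected valid: 100 / 0.87 = 114.9, so 115. The 120 clears this and the 100 does not. With valid cases distributed as Binomial(n, 0.87), the chance of at least 100 valid is about 0.90 for n = 120. For n = 100 it is 0.87^100, about 0.0000009.

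**6. Effect on precision.** The documents give no expected AUC, so I assume 0.75 or 0.85 for ME/CFS against all others, with the Hanley–McNeil standard error. With 35 and 69 valid cases (the 120 version), the 95% half-width is 0.105 or 0.086. With 27 and 60 (the abstract's version, in the recruitment proportions), it is 0.118 or 0.098.

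**The case against.** The strongest reply is that the split in the Aim 3 section is plainly the worked-out one. It has counts for every group, they reconcile exactly with recruitment, and 120 is large enough to absorb a 13% loss and still leave 100. On that view the abstract needs a one-line correction. Much of this stands. It also defeats a broader reading that a reader might reach, namely that neither split allows for invalid data: the 120 version does leave enough valid cases, although the article does not say that this was its purpose. What the reply does not remove is that both versions are in force, that the abstract's version falls short of the cited 100, and that the counts are unlabelled and cannot all be valid cases.

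A reader might also infer something stronger from *Progress and plan*: "We will start preliminary analysis in July 2022 and disseminate preliminary results in October 2022", with 110 participants recruited by 20 May 2022. The inference would be that the split is not locked beforehand, that validation cases will already have been examined, and that the independent validation promised under Aim 3 is lost. The documents do not support this. The article does not say when the split is drawn, and a condensed article may leave that to a fuller plan. It does not say that the preliminary analysis touches Aim 3; the comparisons in Aims 1 and 2 do not depend on the split. The ROC curve is still to come from a separate validation group. Any count of early participants who would later fall in the validation set would need the group mix of the 110 and the timing of the split, and neither is given. HRF features do serve both Aim 1 and Aim 3, which makes a clarifying sentence worth asking for, but silence is not an error.

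**Conclusion.** Wrong as written. A primary aim has two test-set sizes, 100 and 120, and both splits allocate 288 where the plan expects about 251 valid. Under the plan's own 87%, the 120 version gives about 104 valid validation cases and meets the cited 100 with little margin; the abstract's version gives about 87 and does not.

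The practical loss is modest: about 17 fewer valid test cases (104.4 − 87.0 = 17.4), and an AUC interval wider by roughly 0.01 on each side under the assumed AUCs. The main harm is that the planned validation is not fixed to one number.

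The valid counts assume that the 13% loss falls equally on all groups and on both parts of the split, and the probabilities also assume independent losses. The figure of 251 is taken as stated; the contradiction between the two splits does not depend on it.

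**What to change.** State one split in both the abstract and the Aim 3 section, and label the counts as recruited or valid. The simplest version is to correct the abstract to 168/120 recruited and add that about 146/104 are expected to be valid at 87%, stratified by group with the validation set at about 35/17/35/17. Stating recruited counts with expected valid counts beside them is workable because some invalid data are identified only after the study ends. If another split is preferred, it should keep at least 100 valid validation cases, which means at least 115 allocated.

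As a clarification only, add a sentence saying that validation cases are kept out of any preliminary neuromarker or feature-selection work.

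The cost is wording in two or three places. The clarification, if adopted, leaves somewhat fewer cases for that preliminary work.

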### Data analysis plan

The measured variables will firstly be tested for normal distribution. Equivalent non-parametric methods will be used if any variable does not exhibit a normal distribution. The activity measure, body mass index, age, depression, and anxiety will be included as covariates for all statistical analyses. The false discovery rate (FDR) will be used to correct for multiple comparisons.

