### Controlling confounding factors

ME/CFS is an illness currently defined by consensus criteria and questionnaires completed by patients. Thus, there is a risk of an ill-defined ME/CFS patient cohort. The proposed study will mitigate this problem by following CCC ME/CFS criteria and diagnosis agreed by two experienced clinicians ([name] and [name]).

Patients with ME/CFS or fibromyalgia may have ongoing medications, which is logistically unavoidable for the study. We mitigate this risk by following steps. (1) Individuals using marijuana or substance were excluded because their known alteration of brain structure and function. (2) Each medication will be determined individually by agreement of investigators ([name], [name] and [name]) on whether it affects the NVC. We include individuals on medication that does not affect the NVC. (3) Two clinicians ([name] and [name]) will assess individuals on medication affecting the NVC to determine if it is safe to stop medication for 3 weeks. Individuals considered safe to stop medication will further seek professional opinions from their caring physicians and then stop medication 2 weeks before and 1 week after MRI. We will exclude individuals who are at risk to stop medication affecting the NVC.

Both ME/CFS and fibromyalgia predominantly affect females (39). Thus, we may recruit more females than males. Indeed, our current sample includes 82% female and 18% male in all groups, including HCs. This unequal sex ratio risk cannot be avoided because of diseases' inherent features. We will include sex as a covariate in all statistical analyses.

This project started when the severe acute respiratory syndrome coronavirus 2 (SARS-CoV-2) occurred before the long Covid (post-acute sequelae of SARS-CoV-2 infection) was recognized. We decided to keep the study protocol and follow the CCC ME/CFS criteria while considering SAR-CoV-2 as an infection similar to other infections that occurred before the manifestation of ME/CFS.

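### Covariates are promised for every analysis, but the Aim 3 text states no way for them to enter, so the validation ROC alone cannot separate an ME/CFS signature from brain correlates of age, BMI, activity or mood

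*Protocol article*

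**What the plan says.** The general rule opens the Data analysis plan: "The activity measure, body mass index, age, depression, and anxiety will be included as covariates for all statistical analyses". The Abstract (Methods and analysis) gives the same rule with sex added: "The activity measure, body mass index, sex, age, depression, and anxiety will be included as covariates for all statistical analyses". The recruitment section repeats it for activity ("The recorded activity level will be included as covariates for all statistical analyses") and Controlling confounding factors repeats it for sex ("We will include sex as a covariate in all statistical analyses").

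The recruitment section also gives a reason for concern about activity: "there is a risk of identifying brain structural or functional differences from ME/CFS sequelae, rather than from the illness per se". It answers first by choosing sedentary healthy controls, then by the activity covariate.

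The Aim 3 section proceeds in steps: random split, voxel-wise maps, LASSO-PCR on each imaging measure, integration by a deep Boltzmann machine (DBM), pruning of clusters, and a ROC curve. On inputs it says: "Each MRI measure (GM and WM density map, HRF features, etc.) will be entered as input for least absolute shrinkage and selection operator". On performance it says: "The receiver operating characteristic (ROC) curve of the identified neuromarker will be determined using data from the validation group". The split is stated "as well as a validation group (120 samples from 40 ME/CFS, 20 fatigue conditions, 40 HCs, and 20 fibromyalgia"). No step names a covariate, an adjustment of the maps, a covariate-only comparator or an adjusted ROC.

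**The concern.** For Aims 1 and 2 the general rule has an obvious place to act, because both use ANCOVA. LASSO-PCR, a DBM and a ROC curve have no such built-in place, so the reader cannot tell how the rule is carried out for Aim 3.

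This matters because Aim 3 is a primary aim and claims a diagnostic marker made of brain features. A classifier fed with brain maps may use any pattern that differs between groups, including patterns that track age, BMI, inactivity or mood. Two features make such differences plausible. Depression is an exclusion for healthy controls but is not among the mental disorders listed as exclusions for everyone. ME/CFS patients are described as less active because of their illness. LASSO-PCR is also trained to predict disease severity, which may itself track inactivity and mood.

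Holding data out does not protect against this. A random split of one cohort reproduces the same imbalance in the model and validation parts. A validation AUC above 0.5 would then show that the groups can be told apart, but not that the imaging carries ME/CFS information beyond the covariates.

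**Working it through.** **Step 1: the places side by side.**

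| Place in the protocol article | What it fixes |
|---|---|
| Abstract; Data analysis plan; recruitment section; Controlling confounding factors | Covariates in all statistical analyses (the Data analysis plan list omits sex) |
| Group difference sections (Aims 1 and 2) | ANCOVA, where covariates can enter directly |
| Aim 3 section | Imaging measures as input, ROC in the validation group, no covariate step stated |

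**Step 2: the split.** By group, 51 + 40 = 91 ME/CFS, 41 + 20 = 61 fatigue, 51 + 40 = 91 healthy controls and 25 + 20 = 45 fibromyalgia; 168 + 120 = 288. The Aim 3 split therefore agrees with the recruitment targets and is used below. (The Abstract gives 188 and 100; the argument does not depend on which is used.)

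**Step 3: null precision of the AUC.** The Hanley-McNeil variance is [A(1−A) + (m−1)(Q1−A²) + (n−1)(Q2−A²)]/(mn), where Q1 = A/(2−A) and Q2 = 2A²/(1+A). At A = 0.5, Q1 = Q2 = 0.3333, so each difference from A² is 0.0833.

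- ME/CFS against all others, 40 v 80: [0.25 + 118 × 0.0833]/3200 = 10.083/3200, SE 0.056.
- ME/CFS against healthy controls, 40 v 40: [0.25 + 78 × 0.0833]/1600 = 6.75/1600, SE 0.065.

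The text does not say which contrast the ROC uses, so both are shown.

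**Step 4: AUC from a covariate alone.** The article gives no group differences on covariates, so d and r are assumptions. Let the groups differ by d SD on one covariate, and let the MRI score carry no disease signal but correlate r with that covariate. Then AUC = Φ(r·d/√2).

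| d (SD) | r = 0.7 | r = 1.0 |
|---|---|---|
| 0.2 | 0.54 | 0.56 |
| 0.3 | 0.56 | 0.58 |
| 0.5 | 0.60 | 0.64 |
| 0.8 | 0.65 | 0.71 |

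For example, d = 0.5 and r = 0.7 gives Φ(0.35/1.414) = Φ(0.247) = 0.598; d = 0.8 and r = 1.0 gives Φ(0.566) = 0.714.

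**Step 5: distance from 0.5.** If d applies to the whole contrast, 0.598 to 0.714 lies 0.098/0.056 = 1.75 to 0.214/0.056 = 3.8 null SEs above 0.5 for 40 v 80, and 0.098/0.065 = 1.5 to 0.214/0.065 = 3.3 for 40 v 40.

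**Step 6: dilution by the disease groups.** If only the healthy controls differ from ME/CFS on the covariate, and the 20 fatigue and 20 fibromyalgia participants do not, the 40 v 80 AUC is the average of the two halves. The range becomes (0.598 + 0.5)/2 = 0.549 to (0.714 + 0.5)/2 = 0.607, or 0.9 to 1.9 SEs. The comparison groups thus give real but partial protection in the pooled contrast, and none in the contrast with healthy controls.

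**The case against.** The strongest reply is that the general rule stands at the head of the whole Data analysis plan and so nominally covers Aim 3. The Aim 2 section names no covariate either and relies on the same preamble. How adjustment enters a machine-learning pipeline is detail that an article may leave to a fuller document. This stands to the extent that one cannot say covariates are left out of Aim 3, or that two rules contradict each other. What remains is that a rule stated as universal is followed by a step-by-step procedure in which it has no evident place, in an article that gives fuller reporting of analysis plans as its purpose.

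A reader might also infer that the rule, taken literally, makes HADS scores and actigraphy inputs to the classifier. The document does not support this. The primary outcomes section defines the neuromarker as brain features from several MRI modalities, and a covariate is not a predictor of interest.

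Design controls count as well. Controls are sedentary, age is limited to 18–65 and BMI above 35 is excluded. The fatigue and fibromyalgia groups are there for specificity. Sex is a weak example, because the article reports 82% female and 18% male in all groups including controls (an interim figure, and the wording could mean the pooled sample). But restriction is not matching, and none of these measures deals with depression and anxiety.

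Finally, activity and mood may be consequences of the illness, so demanding that MRI add to them could discard genuine disease signal. This is a sound objection to resting the whole Aim 3 claim on that gain, and the fix allows for it.

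**Conclusion.** The point holds as a gap in specification with a real consequence for interpretation. As written, an unadjusted validation ROC from a random split of one cohort, with no matching described, cannot separate an ME/CFS brain signature from brain correlates of age, BMI, residual activity differences, or depression and anxiety.

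The size is unknown. The range of about 0.60 to 0.71 rests on an assumed difference of 0.5 to 0.8 SD in a single covariate and on r between 0.7 and 1.0. Smaller differences of 0.2 to 0.3 SD give 0.54 to 0.58, which is hard to tell from chance at these sample sizes. The r = 1.0 figures are upper bounds for one covariate, since they assume that MRI encodes it perfectly.

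A reader might go further and take a 1.0 SD depression difference against healthy controls, AUC Φ(1/√2) = 0.76, as 0.26/0.056 = 4.6 SEs above chance. That divides a 40 v 40 contrast by a 40 v 80 SE; on 0.065 it is 4.0, and it again assumes perfect tracking. The documents give no basis for saying that confounding of this size is present. No stated figure in the plan changes.

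**What to change.** In the Aim 3 section:

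1. State how the general covariate rule applies, and that covariates are not inputs to LASSO-PCR or the DBM. List sex with the other covariates in the Data analysis plan.
2. Fit a covariate-only classifier (age, sex, BMI, activity, HADS) in the model group.
3. In the validation group, report the covariate-only AUC, the neuromarker AUC, and the gain from adding the neuromarker to the covariates. Do this overall and for ME/CFS against each comparison group.
4. Interpret the neuromarker AUC against the covariate-only AUC, not against 0.5 alone.
5. Show the gain over age, sex and BMI separately from the gain that also includes activity and HADS, because the latter may be consequences of the illness.

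The cost is one low-dimensional model on data already collected, plus wording. The headline may look less favourable, and the increment will be imprecise, above all against the fatigue and fibromyalgia groups with 20 validation participants each.
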